### Background variables

Adolescents report their gender, age, country of birth, and family composition, and migrant students also report migration status, the reason for migration, time in the host country, and separation of family members during migration. Teachers report their gender, age, teaching background, and the number of students they teach. Parents report their gender, age, marital status, number of children in a household, employment situation, education, and subjective income, and immigrant parents also report migration status, the reason for migration, time in the host country, and separation of family members during migration.

The categories for natives, immigrants, and refugees will be formed using the question reason for migration. Natives will be categorized as those who are born in Finland. Immigrants will be categorized as those who respond they had come to Finland because of their parents’ temporary or permanent work. Refugees will be categorized as those who report they were fleeing war, persecution, or danger.

## Analytic strategy

Due to the sampling procedure, our data will be clustered in two levels: pupils are nested in 134 classes, and classes in 16 schools. The data contains variables from individual, class, and school levels, and the interventions are given at the school level. All the indicators of outcome variables are measured at all three time points at the individual level. T1 was collected before the intervention, T2 20 weeks after the intervention started, and T3 as a follow-up 52 weeks after the beginning of the intervention. We expect the intervention to change the levels in outcomes from T1 to T2, and the new levels to remain the same through T3 follow-up.

The structure of the data requires the use of structural equation (SEM) methods combining longitudinal, multi-level, path analytic models with confirmatory factor analysis. The psychometric properties of the outcome variables, including measurement invariance between time points T1, T2, and T3, are tested before constructing summary scales using the most reliable items. The scales are then specified as manifest variables in the models. Alternatively, latent constructs are used, depending on the complexity of the final model specifications. The core model in all our analyses will be a version of latent growth curve model [72, 73], that is also known as intervention model [74] due to the coding of the fixed parameters in the model, which are responsible for the shape of the constant growth trajectories at the individual level (the 1’s in Fig. 2). The latent growth parameters will be estimated with the Mplus 8.0 software using a robust maximum likelihood estimator (MLR), which allows non-normal continuous indicators to be reliably analyzed. Additionally, MLR is a full-information estimator allowing the use of missing data without any separate imputations. The validity of the MAR assumption is scrutinized, and if needed, auxiliary variables predicting missingness will be added into the models. Demographic and baseline characteristics will be summarized using means and standard deviations for quantitative variables and percentages for categorical variables.

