## Study setting and participants

Power calculations were conducted before the data collection started. With alpha set at 0.05, power at 0.80, and rho = 0.05 (the intra-cluster correlation), a sample size of at least 40 clusters (i.e., schools) with 25 youths each was identified as necessary. Therefore, 500 youths per study arm (i.e., intervention or wait list control) were needed, resulting in 1500 total participants. To account for an expected drop-out rate of 20%, 1800 youths would have been recruited in total. To facilitate the recruitment of so many participants, recruitment was split between the Finnish study team and our team partners in Sweden.

The interventions were implemented in lower secondary schools with grades 7–9 and/or introduction classes for newcomer youth. We focused on immigrant youth who have resided in Finland for less than 6 years. Figure 1 presents the flowchart of the recruitment. Seventeen schools expressed their interest in participating in the study, but after allocation, one school dropped out. According to the randomization, eight schools were allocated into the INSETT+TRT intervention, three schools were allocated into PIER, and five schools served as waiting list controls. Also, Fig. 1 reports the numbers of students, teachers, and parents who answered the survey in the first round of data collection.

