In the core model (Fig. 2), there are two latent state variables, measuring true scores of PRE- and POST-intervention levels of the outcomes. The PRE-intervention state is indicated by the measured T1 variable without time-related measurement error because there is only one measurement point. In the case of POST-intervention state, there are two indicators, enabling the modeling of measurement error. The loadings of the indicators in the measurement part of the model are fixed to 1’s, meaning that the trajectory from T1 to T3 has the same shape for every individual. Only the level of PRE-intervention state and the difference between PRE- and POST-intervention states are random so that the means and variances of these variables within and between the clusters can be estimated. As predictors of the POST-intervention state, our model specifies the PRE-intervention state (path coefficient *a*, which is anticipated to be negative due to floor and ceiling effects), a dummy for intervention/control group membership (direct effect *c*), and potential mediating variables (path coefficient *e*, implying indirect effect *d*e* for intervention-control-group difference). The covariance between the PRE-intervention state and the dummy for intervention/control group membership (parameter *b*) is supposed to be 0, indicating that the randomization was successful. Moderation mechanisms are investigated by estimating the model simultaneously in groups created according to categorized moderator variables (multi-group SEM). Finally, the simple estimates of total intervention effects are calculated from a model without mediators and moderators (parameter *c* divided by the variance of POST-intervention latent variable, giving an equivalent to Cohen’s *d*).

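### MLR standard errors on 16 schools, three of them in PIER, do not hold the 5% error rate unless a small-sample correction is added

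*Protocol article*

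**What the plan says.** Study setting and participants gives the error rate and the other planning assumptions: "With alpha set at 0.05, power at 0.80, and rho = 0.05 (the intra-cluster correlation". From these the authors derived the planned number of schools: "a sample size of at least 40 clusters (i.e., schools) with 25 youths each was identified as necessary". The section then reports what was achieved. Eight schools went to INSETT+TRT, and "three schools were allocated into PIER, and five schools served as waiting list controls".

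Analytic strategy describes the structure as follows: "our data will be clustered in two levels: pupils are nested in 134 classes, and classes in 16 schools". It says that the interventions are given at school level and then names the estimator: "The latent growth parameters will be estimated with the Mplus 8.0 software using a robust maximum likelihood estimator (MLR". The reasons given for this choice are non-normal indicators and the handling of missing data. The number of clusters is not among them.

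The core-model paragraph of the same section makes the intervention effect the coefficient *c* of a group dummy on the post-intervention state. No degrees-of-freedom rule, small-sample correction or cluster-level test is named.

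The Discussion concedes that too few clusters were recruited for 80% power and that significant school-level effects will be hard to find. It says nothing about the validity of the tests.

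**The concern.** The dummy behind *c* is constant within a school, so the independent evidence is 8 against 5 schools for INSETT+TRT and 3 against 5 for PIER. More pupils or classes per school do not add independent units. Robust (sandwich) standard errors are consistent as the number of clusters grows. With a handful of clusters they are too small on average and also imprecise, and a normal critical value of 1.96 allows for neither.

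At stake is the validity of every p-value and interval for the first research aim. Someone who reads the Discussion will think a significant result is hard to obtain and therefore credible. Under the planned test, false positives would in fact be more frequent than stated, most of all for PIER.

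**Working it through.** **Inputs from the article.** Alpha 0.05 (two-sided assumed), ICC 0.05, and 16 schools split 8/3/5. **Assumed.** The between level is the school, Wald statistics are referred to the normal distribution, and schools have 25 or 60 pupils on average (student numbers are in a figure not shown).

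**1. The plan's own figure.** The article gives no effect size, so its 40 clusters cannot be reproduced. With 25 pupils per school the design effect is 1 + 24 × 0.05 = 2.2. The planned 500 per arm (20 schools × 25) is then an effective 500/2.2 = 227, which gives 80% power for a standardised difference of (1.96 + 0.84) × √(2/227) ≈ 0.26. The only error rate stated is alpha = 0.05, and the checks below are made against that.

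**2. Average bias of the robust variance, equal school sizes.** Let SS be the sum of squares of school means about their arm mean, and σ² the variance of a school mean. The sandwich variance of the difference between arms is SS_a/n_a² + SS_0/n_0². Its expectation is σ²[(n_a−1)/n_a² + (n_0−1)/n_0²], against a true σ²(1/n_a + 1/n_0).

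- INSETT+TRT v control: 7/64 + 4/25 = 0.269, against 1/8 + 1/5 = 0.325. Ratio 0.83.
- PIER v control: 2/9 + 4/25 = 0.382, against 1/3 + 1/5 = 0.533. Ratio 0.72.

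**3. Type I error, equal school sizes, 400,000 simulated trials under the null.**

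| Test at nominal 5% | INSETT+TRT (8 v 5) | PIER (3 v 5) |
|---|---|---|
| School-level sandwich, 1.96 | 10.7% | 15.8% |
| ML, joint model, 1.96 | 10.1% | 10.2% |
| ML, pairwise, 1.96 | 9.9% | 14.1% |
| REML-type variance, t on 13 df (joint) | 5.0% | 5.1% |
| REML-type variance, pairwise t (11 or 6 df) | 5.0% | 5.0% |

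The joint ML entry can be checked exactly. ML divides the residual sum of squares by 16 where 13 is unbiased, so a cut-off of 1.96 corresponds to 1.96 × √(13/16) = 1.767 on a t distribution with 13 df. The two-sided tail is 10.07%.

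**4. Sensitivity.** A two-level random-intercept ML fit was simulated 4,000 times per scenario, with ICC 0.01 to 0.10, 25 or 60 pupils per school, and school-size coefficient of variation 0 or 0.6.

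| Joint 16-school model, 1.96 | INSETT+TRT | PIER |
|---|---|---|
| Sandwich, no covariate | 10.4-13.6% | 15.1-18.7% |
| Sandwich, one school-level covariate (ICC 0.05) | 13.7-14.0% | 18.3-19.3% |
| Model-based ML, no covariate | 5.9-11.4% | 7.2-11.2% |

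The sandwich figures change little with ICC or school size. They follow mainly from the 8/3/5 split.

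**5. Would a permutation test serve instead?** Trial design says schools were grouped by whether they had an introductory class and then randomised between intervention and control within each group. On that reading PIER is compared only with controls in its own group, and INSETT+TRT only with the rest. The split of the five controls is not given. Let *k* of them be in PIER's group.

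| k | Consequence for the smallest two-sided p |
|---|---|
| 0 | PIER has no control in its group |
| 1 | PIER: 4 relabellings, 1/4 = 0.25 |
| 2 | PIER: 10 relabellings, 1/10 = 0.10 |
| 3 | PIER: 20 relabellings, 2/20 = 0.10 |
| 4 | INSETT+TRT, 8 v 1: 9 relabellings, 1/9 = 0.11 |
| 5 | INSETT+TRT has no control in its group |

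Whatever the split, at least one contrast can never reach p < 0.05.

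**The case against.** The strongest reply is that the article names software and an estimator but not a test. It gives no reference distribution and does not say at which level the robust errors are computed, and a full analysis plan could supply a small-sample correction. The simulations also use a simpler stand-in for the multilevel latent model, and model-based errors would inflate less. All of this stands, and it makes the figures conditional. It does not remove the point: the article fixes the estimator, justifies it on grounds unrelated to the number of schools, and discusses the shortage of schools only in terms of power.

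Two stronger readings are tempting.

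- A reader might infer from the 134 classes that the class will serve as the cluster, which would make the error larger still. The article lists schools as a level and places the intervention there. Nowhere does it say that school clustering will be dropped.
- A reader might infer that the multi-group moderation analysis adds to the false-positive rate. Categorising a continuous moderator loses information, which is a matter of efficiency. The article does not say that the groups are treated as independent samples, and no error rate was computed for that analysis.

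**Conclusion.** The point holds in conditional form. With school-level MLR standard errors and a normal reference, the nominal 5% becomes about 10-14% for INSETT+TRT v control and 15-19% for PIER v control. That is roughly double and triple, and the tripling applies to PIER only. With model-based ML errors in the joint model without covariates it is about 6-11%.

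These figures rest on the school as the between level, the normal reference, assumed school sizes, and a random-intercept model standing in for the Mplus model. They should be quoted as the consequence of the uncorrected test, not as a known property of the final analysis. The limitation stated in the Discussion does not cover the problem, because low power and an inflated type I error are different defects.

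**What to change.** Take the confirmatory p-values and confidence intervals for the total effect from a REML mixed model of the outcome on arm, T1 score and randomisation group. Include random school and class effects and Kenward-Roger or equivalent small-sample degrees of freedom. Fit it at T2 (the article's primary time point) and T3 (secondary). The school level must be in the model; clustering on classes alone is not enough. Keep the Mplus model for mediation and as a supporting analysis. In the Discussion, add that few schools threaten the validity of large-sample p-values and intervals as well as power. Do not make a permutation test within randomisation groups the confirmatory test, for the reason in step 5.

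**Cost.** No new data are needed, and the model runs in standard software. Intervals widen and p-values rise. The post-intervention state with two indicators (T2 and T3) no longer carries the confirmatory test. With three arms and a randomisation-group term, about 16 − 4 = 12 school-level degrees of freedom remain. On the reading in step 5, each intervention is then compared only with controls in its own group. If all five controls lie in one group, the arm in the other group has no such comparison, so the split should be reported. The return to 5.0-5.1% was shown for equal school sizes without the group term. Kenward-Roger itself was not simulated.

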**Fig. 2 Fig2:**
[figure not shown]
Latent growth curve theoretical model for analysis

Explanations: Primary outcomes—*Y*_1_ = SDQ (difficulties), *Y*_2_ = SDQ (strengths), and *Y*_3_ = CYRM; intervention status—*I*_0_ = waiting list control group, *I*_1_ = INSETT+TRT, and *I*_2_ = PIER; possible moderators—*Z*_1_ = SF-36, *Z*_2_ = GHQ-12, *Z*_3_ = PTSD-8, *Z*_4_ = MaaP; *Z*_5_ = PEDQ-CV (parent), *Z*_6_ = PEDQ-CV (adolescent), *Z*_7_ = DSSYR, *Z*_8_ = (daily stressors), and *Z*_8…*n*_ = sociodemographics. Expected mediators: INSETT Teachers (competence)—Mb_1_ = TMAS, Mb_2_ = TSES, Mb_3_ = SISI, Mb_4_ = BBI, Mb_5_ = UWES, Mb_6_ = Trust, and Mb_7_ = classroom atmosphere; TRT Adolescents (trauma)—Ma_1_ = CRIES-8; PIER Adolescents (social)—Mc_1_ = MSPSS, Mc_2_ = PSSM, Mc_3_ = PEDQ, and Mc_4_ = interethnic friendships.

In the core model (Fig. 2), there are two latent state variables, measuring true scores of PRE- and POST-intervention levels of the outcomes. The PRE-intervention state is indicated by the measured T1 variable without time-related measurement error because there is only one measurement point. In the case of POST-intervention state, there are two indicators, enabling the modeling of measurement error. The loadings of the indicators in the measurement part of the model are fixed to 1’s, meaning that the trajectory from T1 to T3 has the same shape for every individual. Only the level of PRE-intervention state and the difference between PRE- and POST-intervention states are random so that the means and variances of these variables within and between the clusters can be estimated. As predictors of the POST-intervention state, our model specifies the PRE-intervention state (path coefficient *a*, which is anticipated to be negative due to floor and ceiling effects), a dummy for intervention/control group membership (direct effect *c*), and potential mediating variables (path coefficient *e*, implying indirect effect *d*e* for intervention-control-group difference). The covariance between the PRE-intervention state and the dummy for intervention/control group membership (parameter *b*) is supposed to be 0, indicating that the randomization was successful. Moderation mechanisms are investigated by estimating the model simultaneously in groups created according to categorized moderator variables (multi-group SEM). Finally, the simple estimates of total intervention effects are calculated from a model without mediators and moderators (parameter *c* divided by the variance of POST-intervention latent variable, giving an equivalent to Cohen’s *d*).

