Concerning INSETT, we hypothesize that participation of teachers increases their multi-cultural awareness, sense of self-efficacy, and work engagement and decreases their work stress, which in turn are associated with the decreased internalizing and externalizing symptoms and increased prosocial behavior and resilience among the adolescents.We hypothesize that adolescents’ participation in PIER intervention is associated with their increased social support, feeling of belongingness, number of inter-ethnic friendships, and satisfaction on friendships, which in turn is associated with decreased internalizing and externalizing symptoms and increased prosocial behavior and resilience.We hypothesize that adolescents’ participation in TRT intervention is associated with decreased PTSD symptoms of intrusion and avoidance, which in turn is associated with decreased internalizing and externalizing symptoms and increased prosocial behavior and resilience.How do parent- and adolescent-related factors moderate the effectiveness of the two arms of school-based psychosocial interventions of INSET+TRT and PIER?
We hypothesize that good parental mental health and parents’ high sense of competence and confidence in parenting are associated with a statistically significant positive intervention-induced change in adolescents’ mental health (i.e., decreased internalizing and externalizing symptoms and increased prosocial behavior and resilience).We hypothesize that adolescents who report the low frequency of daily stressors and low perceived discrimination show more statistically significant positive intervention-induced change in their mental health (i.e., decreased internalizing and externalizing symptoms and increased prosocial behavior and resilience).

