## Data collection and management

Survey data is collected online from students, teachers, and parents, and informed consent is collected both on paper and online at the beginning of the survey. Foreign-speaking parents receive both online and paper surveys, and the informed consent form is both on paper and online. The online survey is managed using a secure online survey tool [49], and all identifiable information will be stored separately from the research data. The researcher team will collect informed consent first in schools and later via mail. To avoid attrition, participants will receive a personal invitation via e-mail and two reminders to answer the post-intervention (T2) and follow-up (T3) surveys. The RWS consortium will manage and store the research data and will have a common data management plan available online.

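### Grouping students by parent-reported moderators drops every student without parent data, and full-information estimation does not prevent it

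*Protocol article*

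**What the plan says.** The last paragraph of the Analytic strategy fixes the method for moderation: "Moderation mechanisms are investigated by estimating the model simultaneously in groups created according to categorized moderator variables (multi-group SEM". The legend to Fig. 2 lists the possible moderators. Z1 to Z5 are the SF-36 item, GHQ-12, PTSD-8, MaaP and the parents' version of the PEDQ-CV, and Table 2 confirms that parents report them. The Objectives attach a hypothesis to this group, namely that "good parental mental health and parents’ high sense of competence and confidence in parenting are associated with a statistically significant positive intervention-induced change" in the adolescents.

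For missing data the Analytic strategy states that "MLR is a full-information estimator allowing the use of missing data without any separate imputations", and adds: "The validity of the MAR assumption is scrutinized, and if needed, auxiliary variables predicting missingness will be added into the models". No other handling of missing values is described.

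Under Data collection and management, "Survey data is collected online from students, teachers, and parents", so parents answer their own questionnaire. Under Eligibility criteria, students face no exclusion criteria beyond giving consent. A student can therefore have outcome data and no parent score.

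**The concern.** Two fixed choices do not fit together for the parental part of the third aim. Full-information likelihood uses incomplete records when the missing values belong to variables inside the model. A grouping variable is outside it: the model is conditional on group membership. A student without a parent score cannot be placed, so the analysis of parental moderation becomes an analysis of students whose parents replied.

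At stake are the precision of a subgroup contrast in a trial whose Discussion already concedes insufficient power, and the population to which the parental result applies. A reader of the missing-data sentence would not expect this loss.

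**Working it through.** **Step 1: the likelihood.** With groups g formed from the categorized moderator Z, the log-likelihood is the sum over g of the sum over students with Z = g of log f(observed y | parameters of group g). If part of y is missing, the student still contributes the density of what was observed. If Z is missing, the student is in none of the inner sums. An auxiliary variable enlarges y and does not assign Z. A separate group for students without parent data would keep them in the file but would not place them at any level of the moderator, and the text does not plan one.

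**Step 2: scale.** The protocol gives no figure to reproduce. Parent numbers are in Fig. 1, which is not shown, so the response r below is an assumption. Inputs from Study setting and participants are 500 students per arm (1500 in total), 25 per cluster and an intra-cluster correlation of 0.05. The counts are illustrative, since recruitment fell short of plan. The factors do not depend on the total.

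- Students kept = 1500r. Per arm and half of a two-way split = 500r/2.
- Factor A, no clustering: 1/√r.
- Factor B, arm contrast with the same clusters: √[DEFF(r)/(r × DEFF(1))], where DEFF(r) = 1 + (25r − 1) × 0.05 and DEFF(1) = 2.2.

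| r | kept | per arm and half | A | B |
|---|---|---|---|---|
| 80% | 1200 | 200 | 1.12 | 1.05 |
| 70% | 1050 | 175 | 1.20 | 1.09 |
| 50% | 750 | 125 | 1.41 | 1.20 |
| 30% | 450 | 75 | 1.83 | 1.42 |

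Example for B at 50%: DEFF = 1 + 11.5 × 0.05 = 1.575, and √[1.575/(0.5 × 2.2)] = 1.20. The moderation contrast compares students with different parent scores within the same schools, so a shared school effect largely cancels and A is the closer guide. A 10% rise in standard error occurs below r = 1/1.1² = 0.826 under A, and near 67% under B. Both columns compare with complete parent data, which no analysis can fully restore.

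**Step 3: bias.** One simulation had 400,000 students, two equal arms, a binary moderator, a true moderated effect of −0.30, no clustering and about 48% parent response.

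- All students: −0.298.
- Response depending only on the pre-score, which is in the model: −0.297.
- Response depending on the post-score: −0.261, a shrinkage of 0.037/0.298 = 12%.

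In a second simulation (n = 1000, 50% response strongly dependent on the moderator, true interaction −0.30), all students gave −0.303 and respondents −0.304. In a third, at about 50% response depending on the moderator, the contrast between dichotomized groups shrank from −0.47 to −0.43. The likely reason is that selection shifts the mean moderator value inside each coarse category.

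**Step 4: what a remedy recovers.** In the second simulation the standard error of the interaction was 0.089 with complete data, 0.142 in respondents and 0.137 after imputation. That closes 0.005/0.053 = 9% of the gap. In the third, under random non-response, the ratio of estimate to standard error was 3.0 for the planned grouping in respondents, 3.9 for a continuous interaction in respondents, and 4.1 with compatible imputation (SD falling from 0.077 to 0.070). Most of the gain comes from not categorizing, and imputation adds a little. All these settings are assumed, so the results show direction and rough order only.

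**The case against.** The strongest reply is that the full-information sentence describes the estimator of the latent growth model and is true there. Nowhere does the article say that all students enter the parent-moderator models. On this view only an unstated detail remains, of the kind a condensed article leaves to the analysis plan. The first part stands: this is no literal contradiction, and the sentence is right for outcomes. The second does not. The article names the grouping method and an estimator without imputation, and together these determine what happens to a student with no parent score.

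A reader might infer that losing students whose parents are distressed or not fluent, the poor-health end of the moderator, in itself biases the contrast. The material does not support that. The model conditions on the moderator, and selection on it left the interaction unchanged in the second simulation. Nor do the documents show that such parents reply less often, and foreign-speaking parents are sent the survey both online and on paper.

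It is also fair that a baseline parent reply precedes the post-score and cannot be caused by it. The two can still share causes. The respondents' result then differs from that for all students if those causes also modify the effect, or if parent response differs by arm.

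Finally, imputation relies on data being missing at random given the student data. If parents stay silent because of the moderator itself, the respondents-only interaction may be the safer estimate. This is a reason to report both.

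**Conclusion.** The point holds within limits. As written, the method removes students without parent data from every analysis moderated by Z1 to Z5, and neither full-information MLR nor auxiliary variables prevents it. Only the parental part of the third aim is touched, because total effects come from a model without moderators. It should be corrected, but it does not threaten the main comparison.

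The firm consequences are lower precision and a result restricted to students with responding parents. On factor A the standard error rises by 12% at 80% response and by 83% at 30%, relative to complete parent data. Bias is conditional: it arises, for example, if response relates to the post-score, or if response varies with the moderator inside coarse categories. Its size in this trial cannot be given without the parent response figures.

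**What to change.** For Z1 to Z5, replace the grouping with the T1 parent score kept continuous and tested through an arm-by-moderator interaction. Either bring the score into the likelihood as a modelled variable, or impute it with a multilevel model compatible with the interaction (school, arm, arm-by-outcome terms, student migration status, family composition, T1 student scores). Report the respondents-only analysis beside it as a sensitivity analysis, and give the number of students lacking parent data by arm. Limit the full-information sentence in the Analytic strategy to modelled outcomes and mediators.

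The cost is additional analysis work and reliance on missing at random given the student data. No new data are needed. The change should not be presented as restoring the lost precision, since imputation returns only a modest part of it.

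### The total-effect model adjusts only for the baseline score and leaves out pupil background and the introductory-class grouping used in allocation

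*Protocol article*

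**What the plan says.** The Analytic strategy section names three kinds of predictor of the post-intervention (POST) state: the PRE state (path a), the intervention dummy (path c) and potential mediators (path e). Moderators enter only as grouping variables in a multi-group model. For the overall effect, "the simple estimates of total intervention effects are calculated from a model without mediators and moderators".

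In the legend to Fig. 2, sociodemographics are the last entry under possible moderators, just before the list of mediators begins: "sociodemographics. Expected mediators: INSETT Teachers (competence". The Background variables section shows that the data exist: "Adolescents report their gender, age, country of birth, and family composition", with migration status, reason for migration and time in the host country added for migrant pupils. Auxiliary variables are allowed in the models, but only if needed to handle missing data.

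The Trial design section says that schools were grouped by whether they offered an introductory class before they were allocated. Three schools that joined later all had introductory classes and were randomised only between INSETT+TRT and control. The result, under Study setting and participants, was that "eight schools were allocated into the INSETT+TRT intervention, three schools were allocated into PIER, and five schools served as waiting list controls".

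**The concern.** Taken together, these statements leave a total-effect model with two terms, PRE and arm. Two kinds of baseline information are left out.

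The first is pupil background. Natives, immigrants and refugees all take part, with no exclusion criteria for students, and the Discussion itself describes immigrant children as having an increased risk of mental health problems. With three to eight schools per arm, randomisation cannot be relied on to balance the mix.

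The second is the school grouping. TRT is aimed at recently arrived refugee youth and PIER at mixed classes, and the grouping came before allocation. Pupil mix may therefore differ between arms by design, not only by chance. A factor that restricts allocation normally belongs in the model.

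At stake are the credibility of parameter c as an answer to the first aim, and some precision in a trial that already reports too few clusters.

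**Working it through.** **Inputs from the article.** The planning values are "With alpha set at 0.05, power at 0.80, and rho = 0.05 (the intra-cluster correlation" and "a sample size of at least 40 clusters (i.e., schools) with 25 youths each was identified as necessary". Schools per arm are 8, 3 and 5. No effect size, and no association between covariates and outcome, is given.

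**The plan's own figure.** The design effect is 1 + (25 - 1) x 0.05 = 2.2, so 500 per arm is 500/2.2 = 227 effective pupils. Two-sided alpha 0.05 and 80% power then imply a standardised difference of about 0.263. At this value, 227 x 2.2 gives the stated 500 per arm, and 40 x 25 = 1000 is two such arms. This value is back-solved and serves only as a yardstick.

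**Standard error without covariates.** Take ICC 0.05, 25 pupils per school and total variance 1. The variance of a school mean is 0.05 + 0.95/25 = 0.088.
- INSETT+TRT v control: sqrt(0.088 x (1/8 + 1/5)) = 0.169 SD
- PIER v control: sqrt(0.088 x (1/3 + 1/5)) = 0.217 SD

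These figures take no account of PRE.

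**Assumed inputs for the covariates.** Between-school SD of the migrant share 0.10-0.25; gap between migrant and other pupils 0.2-0.4 SD in POST given PRE; 3-5% of within-school variance explained.

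**Between-school variance explained.** (Share SD x gap)^2 runs from (0.10 x 0.2)^2 = 0.0004 to (0.25 x 0.4)^2 = 0.01. Against 0.05, that is 0.8% to 20%.

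**Standard error with pupil covariates.**
- Low end: 0.05 x 0.992 + 0.038 x 0.97 = 0.0865; ratio sqrt(0.0865/0.088) = 0.991
- High end: 0.05 x 0.80 + 0.038 x 0.95 = 0.0761; ratio sqrt(0.0761/0.088) = 0.930

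The fall is about 1-7%: from 0.169 to 0.168-0.157, and from 0.217 to 0.215-0.201. In equivalent schools, 1/ratio^2 gives about 2-16% more.

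**Typical chance imbalance.** Share SD x gap x sqrt(1/k1 + 1/k2):
- 8 v 5: 0.02 x 0.570 = 0.011 to 0.10 x 0.570 = 0.057 SD
- 3 v 5: 0.02 x 0.730 = 0.015 to 0.10 x 0.730 = 0.073 SD

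This comes from the same between-school variance as above, so it must not be added to the precision gain.

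**What PRE leaves behind.** If two pupil groups differ by 0.2-0.4 SD equally at T1 and POST, and POST depends on PRE with an assumed slope of 0.5-0.7, the remaining gap is gap x (1 - slope): 0.2 x 0.3 = 0.06 to 0.4 x 0.5 = 0.20 SD. PRE removes much of the difference but not all. A gap of 0.2-0.4 SD given PRE is therefore a generous assumption.

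**Power.** At 0.263 and without covariates, power is 0.30 (8 v 5) and 0.18 (3 v 5). With 25% of between-school and 5% of within-school variance explained, slightly more than the high end above, it is 0.34 and 0.20.

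**The grouping term.** It uses one school-level degree of freedom: 8 + 5 - 2 = 11 becomes 10, and 3 + 5 - 2 = 6 becomes 5. If each active arm came from one group only, the adjusted contrast also rests on the controls of that group alone. The article does not give the split of the five controls. With an assumed split of 3 and 2, the standard errors would be sqrt(0.088 x (1/8 + 1/3)) = 0.201 and sqrt(0.088 x (1/3 + 1/2)) = 0.271.

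**The case against.** A total effect adjusted for the baseline outcome is a legitimate analysis, and PRE is the strongest single covariate available. No sentence forbids further covariates. The reading joins a label in a figure legend to a sentence about moderators, and leaving moderators out may only mean not splitting the sample. The article is condensed, and a covariate list is often left to the analysis plan. This limits the point: a reader might infer that the plan prohibits adjustment, and the article does not say that. What stands is that the article does list the predictors, gives sociodemographics no role but moderation, and allows auxiliary variables only for missingness.

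The recruitment criterion of 30-50% refugee and immigrant pupils in each class narrows the mix. Over that range the SD of the share cannot exceed 0.10, and it is about 0.06 if uniform. The chance imbalance is then only about 0.01-0.03 SD. That is fair, and it means that wider variation would come mainly from introductory classes, which is why the grouping matters more than any single pupil covariate.

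A reader might also infer a large precision gain. If covariates explained 25-50% of between-school variance, the standard error would fall by 8-17%. Nothing in the article supports that share, the comparison is with a model that lacks PRE, and the migrant-share inputs above reach only 0.8-20%.

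**Conclusion.** The point holds as a modest improvement worth making. As written, the total-effect model adjusts for the PRE state alone and omits both the allocation grouping and the sociodemographics already collected. Differences in pupil mix that the baseline score does not carry remain in parameter c and its error.

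The article does not support calling the estimate biased by a known amount or in a known direction. The 1-7% fall in standard error covers the pupil covariates only. It rests on the assumed migrant-share SD, gap and within-school share, and it combines a gap given PRE with an ICC that takes no account of PRE, so it is an order of magnitude. The shortage of clusters that the Discussion admits is not repaired. The stronger reason for the change is that the analysis should reflect how schools were allocated.

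**What to change.** In the Analytic strategy section, state that the total effect is estimated from a model with:
- the PRE state and the arm terms;
- the introductory-class grouping used in allocation;
- a short fixed set of T1 pupil covariates: gender, age and migration category.

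Add an other foreign-born level to the migration category. The present definitions cover birth in Finland, parental work, and flight from war, persecution or danger, so pupils who came for another reason have no category. If time in Finland is used, enter it as a term that is zero for Finland-born pupils and centred among foreign-born pupils. It does not exist for the Finland-born and should not be treated as missing data. Report the PRE-only model as a sensitivity analysis, and keep the moderation analyses separate.

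The cost is a few more parameters and one school-level degree of freedom for the grouping, with no new data. If each active arm came from one group only, the grouping term may widen the interval, so the number of control schools in each group should be reported with the result.
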